### The Current Study

The aim of this study is to evaluate the efficacy and cost-effectiveness of Psyfit, an online well-being program [39]. The study will add to the existing literature by testing a multi-component and flexible Internet-based intervention to promote well-being. To date, the research in this area is limited to either single interventions focusing on one well-being exercise at a time [28, 36] or to multiple protocol-based interventions [37,38]. In these studies, participants in the intervention groups are allocated to an inflexible intervention, although most people would prefer to choose what they need and feel up to doing [30,40,41]. For this reason, Psyfit offers a choice of different interventions that participants can tailor themselves.

The primary objective of this study is to evaluate the effectiveness of the Psyfit intervention in comparison to a waiting list control group. We hypothesize that the intervention group will demonstrate a significant increase in well-being and a reduction in depressive symptoms at post-test and follow-up compared to the control group. Secondary study objectives are to conduct an economic evaluation and to examine if particular subgroups benefit differently (ie, more or less) than others from the intervention.

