### Assessments

The primary outcome measure is well-being. Secondary outcome measures include depressive symptoms, general health and vitality, and economic costs (as measured by health care use, days of absence, inefficient job performance, and work productivity). For an overview of outcomes and instruments, see Table 1.

Measurements will be taken at baseline (pre-test), directly after the intervention (post-test, 2 months after baseline), and 6 months later (follow-up). All measurements are self-report measures and will be administered via email with a link to the questionnaire on the Internet.

High dropout rates are a characteristic feature of online trials and can be as high as 50% [50]. Therefore, email reminders and rewards (eg, raffle of six iPods and vouchers) for filling in the questionnaires will be used. It is expected that this will lead to a lower attrition rate.

**Table 1 table1:** Questionnaires and assessment times.

		T0	T1	T2
Questionnaire^a^	Measurement	Pre-test	Post-test^b^	Follow-up^c^
MHC-SF	Well-being/positive mental health	X	X	X
WHO-5	Well-being	X	X	X
CES-D	Symptoms of depression	X	X	X
MOS SF-36 subscales	Vitality and general health	X	X	X
TIC-P and PRODISQ	Health service uptake and production losses	X	X	X
CSQ-8	Client satisfaction		X	
Demographics	Age, gender, education, marital status, job status	X		

^a ^all questionnaires are discussed within Instruments section

^b ^2 months after T0

^c ^6 months after T0

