### Instruments

#### Well-Being and Positive Mental Health

Well-being will be assessed with two questionnaires measuring different concepts. The Mental Health Continuum-Short Form (MHC-SF) [51] is a 14-item self-report questionnaire that categorizes measures of well-being as “languishing,” “moderate,” or “flourishing.” Participants rate the items on a 6-point scale from 0 (never) to 5 (every day). The MHC-SF measures subjective well-being as well as psychological and social well-being. These aspects are all addressed in Psyfit; therefore, this questionnaire was chosen. The MHC-SF has shown good internal consistency (> .80) and discriminant validity [44,52].

The WHO-Five Well-being Index (WHO-5) contains 5 positively formulated items on mental health [53]. Participants are asked to rate the items using a 6-point scale ranging from 0 (never) to 5 (all of the time). The WHO-5 has been validated in different populations [53] and is useful as a screening instrument for depression [54]. It was chosen as a measurement instrument because of its brevity and the concurrent validity with depression.

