### Sample Size

Depressive symptoms and well-being are used as a starting point for the power calculation. We aim to be able to show differences between Psyfit and the waiting list control condition with a standardized effect size (Cohen’s *d*) of 0.33 or larger. A standardized effect of 0.33 can be considered as the lower limit of a moderate clinical effect [64] and is based on a meta-analysis of well-being intervention research [35] and a recent randomized controlled trial [36]. To demonstrate this effect, and assuming an alpha of 0.05 and a statistical power (1-Beta) of 80%, we need 145 participants in each condition; therefore, we need 290 participants in total for the trial.

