### Analysis

Results will be reported according to the Consolidated Standards of Reporting Trials (CONSORT) statement regarding eHealth [65,66]. We will adhere to the intention-to-treat (ITT) principle, which means all participants who have been randomized will be included in the analyses. Missing data at T1 and T2 will be imputed using the expectation-maximization (EM) method, as implemented in Statistical Package for the Social Sciences (SPSS) Missing Value Analysis. The program imputes missing values by maximum likelihood estimation using the observed data in an iterative process [67]. In online trials dropout is to be expected, and sometimes a large amount of missing data has to be estimated. Although ITT analysis is the approach of choice according to the CONSORT statement, there may also be pitfalls, such as when the missing-at-random assumption is not plausible and the results of the analysis are subsequently biased [68]. Therefore, a completers-only analysis and a per-protocol analysis will be conducted in addition (sensitivity analysis). Reasons for dropout in the study will be checked at random by telephone follow-up (dropout analysis).

To examine differences between the two conditions, we will use multiple regression analyses with the clinical outcomes on continuous measures (MHC-SF, WHO-5, CES-D, and the vitality and general health scales from MOS SF-36) as dependent variables and an intervention-control group dummy as predictor variable. We will compute standardized effect sizes (Cohen’s *d*). Cohen’s *d *is computed by subtracting the mean post-test intervention score from the mean post-test control group score and dividing the difference by the pooled standard deviation [69].

Moderator analyses will be conducted to examine which groups benefit more (or less) from the intervention by regressing the outcomes on independent variables such as gender, education, mild/moderate depressive symptoms, the treatment dummy, and the interaction with the treatment dummy and the selected independent variables.

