The economic evaluation will be conducted from a societal perspective, thus including the intervention costs (ie, Psyfit), the costs of health care uptake (TIC-P), the participants’ out-of-pocket costs for obtaining health care (TIC-P), and the economic costs due to productivity losses in paid work (PRODISQ). The incremental cost-effectiveness ratio (ICER) will be calculated. Uncertainty in the ICER will be captured using a bootstrap approach, producing a scatter of simulated ICERs over the ICER-plane and by drawing an ICER acceptability curve of the likelihood that Psyfit is more cost-effective for a range of willingness-to-pay (WTP) ceilings.

All analyses will be conducted using two-sided tests and alphas of .05. For this purpose, the most recent version of the SPSS software will be used.

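### No single primary test is fixed: well-being has two instruments and two time points, every test is at .05, and neither natural success rule gives both 5% error and 80% power

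*Protocol article*

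**What the plan says.** All references are to the protocol article.

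- **Assessments** (and the Abstract): "The primary outcome measure is well-being". This names a construct, not a scale. Table 1 schedules MHC-SF and WHO-5 at baseline, post-test (2 months) and follow-up (6 months).
- **Well-Being and Positive Mental Health**: "Well-being will be assessed with two questionnaires measuring different concepts". Neither is ranked above the other.
- **The Current Study**: the hypothesis attached to the primary objective expects a "significant increase in well-being and a reduction in depressive symptoms at post-test and follow-up compared to the control group".
- **Assessments**: "Secondary outcome measures include depressive symptoms, general health and vitality, and economic costs". The Abstract also lists depressive symptoms as secondary.
- **Sample Size**: "Depressive symptoms and well-being are used as a starting point for the power calculation". The calculation uses d = 0.33, alpha 0.05 and 80% power, and arrives at 145 per arm.
- **Analysis**: regressions on the treatment dummy are planned for "MHC-SF, WHO-5, CES-D, and the vitality and general health scales from MOS SF-36", and "All analyses will be conducted using two-sided tests and alphas of .05".

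**The concern.** The primary conclusion can rest on any of four comparisons (two scales at two times), each with its own 5% error rate. Nothing says whether one, some or all of them must be positive. If the results disagree, what counts as success would be settled after the data are seen.

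The status of depressive symptoms adds to this. They are secondary by label, but they stand beside well-being in the main hypothesis and in the basis for the sample size. The section on positive psychology interventions describes one earlier online trial that improved well-being without a significant effect on mental illness, and another that reduced depressive symptoms without improving subjective well-being. If such a split recurred here, the article would not say clearly whether Psyfit had worked.

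**Working it through.** **1. The plan's own figure.** Inputs from Sample Size: d = 0.33, power 80%, alpha 0.05. The Analysis section makes the tests two-sided.

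n per arm = 2 × (1.960 + 0.842)² / 0.33² ≈ 144.1, rounded up to 145. The figure reproduces. The expected z-statistic at 145 per arm is 0.33 × √(145/2) = 2.81, which gives power of 80%. So 290 is the right total for **one** two-sided test at .05.

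**2. Counting the tests.**
- Well-being: 2 instruments × 2 times = 4.
- Well-being at post-test only: 2.
- Well-being plus CES-D at both times: 3 × 2 = 6.

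**3. Any one significant result counts.** With independent tests, the chance of at least one false positive is 1 − 0.95^k:
- k = 2: 9.75%
- k = 4: 18.5%
- k = 6: 26.5%

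The tests are correlated, and the article gives no correlations. I **assumed** 0.5-0.8 between instruments and 0.5-0.7 between times. I then simulated null z-statistics whose correlation matrix is the Kronecker product of the two, and counted draws with any |z| > 1.96.

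| Tests counted as primary | Any false positive | In Psyfit's favour only |
|---|---|---|
| Both instruments, post-test only (2) | about 8-9% | about 4-4.5% |
| Both instruments, both times (4) | about 13-16% | about 6.4-8.2% |
| As above plus CES-D (6) | about 16-22% | about 8-11% |

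The single-test benchmarks are 5% and 2.5%. The result is not very sensitive to the correlations: with one common value for all pairs, four tests give 17.4% at 0.3 and 11.5% at 0.8.

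**4. All results must be significant.** Error is then at most 5%, but power falls. With d = 0.33 on every endpoint (z-statistics centred at 2.81), 145 per arm and the same correlations, the chance that all are significant is about 54-63% for four tests and about 45-58% for six.

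**5. Side by side, for the four well-being tests.**

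| Success rule | Error | Power at 145 per arm |
|---|---|---|
| Any one of four | about 13-16% | at least 80% |
| All four | at most 5% | about 54-63% |
| One named test | 5% | 80% |

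Only the last row matches the Sample Size section.

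**The case against.** The strongest reply is that no inflated error rate is stated anywhere. The hypothesis in The Current Study is worded as a conjunction, and read literally it requires every result to be positive, which does not inflate error. The Analysis section sets alphas test by test and promises no trial-wide 5%. This stands: the error figures hold only under an any-one rule that the article does not state. But the conjunctive reading does not rescue the design, because power then falls well below 80%.

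A reader might infer that the chance of a false primary claim is simply 13-22%. The documents do not support that. Besides the any-one rule, it needs correlations the article does not give, and its upper end counts CES-D as primary although the Abstract and Assessments both call it secondary. It also counts errors in both directions.

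A second reply is that the article leans towards one endpoint. MHC-SF is preferred because Psyfit addresses all the aspects it covers, and it also serves for eligibility. WHO-5 is chosen for brevity and its validity in relation to depression. Cohen's d is defined at post-test. These are hints and not a designation, since the hypothesis also names follow-up. Even two post-test results under an any-one rule give about 8-9%.

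A third reply is that an unseen analysis plan may settle this. A detailed testing order can fairly be left there. The identity of the primary endpoint is core protocol content, however, and the article does state a rule: .05 for every analysis.

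Finally, it would go too far to call disagreement between the two well-being scales likely. The article gives no correlation between them. It is enough that disagreement is possible and that the plan does not resolve it.

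**Conclusion.** The point holds in a conditional form: the primary instrument, time point and success rule are not fixed, and neither natural success rule delivers both the 5% error and the 80% power used in the sample size.

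- **Any one of four suffices:** about 13-16% false-positive error on the primary outcome, given the assumed correlations, with 18.5% under independence. It is about 8-9% if only post-test counts. Errors in Psyfit's favour are about half of each figure, against 2.5%.
- **All four required:** no inflation, but power of about 54-63%, assuming d = 0.33 on each.

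The status of CES-D is a related inconsistency: it is secondary by label but part of the main hypothesis and the power basis. The 16-22% range applies only if CES-D is treated as primary, and should not be quoted as the trial's error rate.

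**What to change.** Before outcomes are compared by arm, name one primary endpoint. MHC-SF total score at post-test is the natural example: the instruments section already justifies the scale, and Analysis defines Cohen's d at that time. Tie the 80% power statement to that endpoint. Label WHO-5, CES-D and all 6-month results as secondary, and align The Current Study and Sample Size with that labelling. The secondary results can be supportive without confirmatory claims, or come under a multiplicity procedure that the sponsor pre-specifies. A fixed testing order is one option but is not needed to cure the defect, and it has a price: one early miss blocks every later claim.

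**Cost.** This changes wording only. Primary error is 5% and 145 per arm remains correct for that test. The trade-off is that WHO-5, CES-D or follow-up results alone could no longer support the primary efficacy claim. For comparison, keeping four co-equal tests under Bonferroni (alpha 0.05/4 = 0.0125) would need 205 per arm for 80% power on each, or leave 62% at 145. Six tests (0.05/6 = 0.0083) would need 223 per arm, or leave 57%.

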## Discussion

This online trial will examine whether an Internet-based self-help intervention for the enhancement of well-being is effective in terms of clinical outcomes and economic costs. A second objective is to examine whether certain groups benefit more or less from the intervention. The enhancement of well-being on a large scale may contribute to public mental health by resulting in better health, fewer mental disorders, and enhanced quality of life on a population level [11,70].

This study has several *a priori *limitations. First, dropout may occur in either of the two groups. To examine any selectiveness, we will conduct dropout analysis and a telephone survey for examining reasons for dropout. Moreover, we will conduct intention-to-treat analyses in which missing values are replaced by their most likely estimates. Second, we will only use self-report questionnaires, not formal diagnostic instruments, to establish diagnoses. Therefore, we will not know whether participants meet the criteria for a Diagnostic and Statistical Manual of Mental Disorders (DSM-IV) diagnosis so results about prevention of mental disorders will not be available. We opted for self-rating because the intervention should be easily accessible and highly applicable because of its public nature. We don’t want to scare people off by intensive diagnostic procedures. A third limitation of this study concerns the use of questionnaires that are not (yet) validated for online purposes. Psychometric properties of online assessments may differ from their paper-and-pencil counterparts [71]. On the other hand, the CES-D [45] and the MHC-SF [52], which are used in this study, have been proven to be reliable and valid instruments even if used on the Internet. Finally, the open recruitment strategy may attract certain groups, for example, more higher-educated people or more spiritually engaged and higher-motivated people. Therefore, care must be taken in generalizing the results.

Our study also has several strengths. It is likely to add to the existing literature because it is—at least to our knowledge—the first evaluation of an online flexible and multiple-component intervention aimed at the improvement of well-being to include people with mild depressive symptoms. As such, we will be able to draw conclusions about the potential impact of such an intervention on mental health. Although the recruitment procedure could be a weakness as previously mentioned, at the same time it creates the opportunity to strengthen external validity (real world implementation potential) by analyzing which target groups are attracted by the “open access” and positively formulated recruitment strategy.

Online interactive programs may attract large numbers of people, therefore, even small or moderate effect sizes can have an impact on population health. If proven to be effective, Psyfit may be an affordable instrument that can be distributed on a large scale to enhance population well-being.

## Abbreviations

CES-D: Center for Epidemiological Studies Depression Scale
CONSORT: Consolidated Standards for Reporting Trials
CSQ-8: Client Satisfaction Questionnaire
DSM-IV: Diagnostic and Statistical Manual of Mental Disorders, Fourth Edition
EM: expectation-maximization
ICER: incremental cost-effectiveness ratio
IP: Internet Protocol
ITT: intention-to-treat
METIGG: Medical Ethics Committee for Mental Health Care
MHC-SF: Mental Health Continuum-Short Form
MOS SF-36: Medical Outcomes Study Short Form (36 items)
PRODISQ: Productivity and Disease Questionnaire
SPSS: Statistical Package for the Social Sciences
TIC-P: Trimbos Institute and Institute of Medical Technology questionnaire for Costs associated with Psychiatric illness
WHO: World Health Organization
WHO-5: WHO-Five Well-being Index
WTP: willingness-to-pay
